## Abstract

**Background:**

Method of levels (MOL) is an innovative transdiagnostic cognitive therapy with potential advantages over existing psychological treatments for psychosis.

**Aims:**

The Next Level study is a feasibility randomised controlled trial (RCT) of MOL for people experiencing first-episode psychosis. It aims to determine the suitability of MOL for further testing in a definitive trial (trial registration ISRCTN13359355).

**Method:**

The study uses a parallel group non-masked feasibilityRCT design with two conditions: (a) treatment as usual (TAU) and (b) TAU plus MOL. Participants (*n* = 36) were recruited from early intervention in psychosis services. Outcome measures are completed at baseline, 10 and 14 months. The primary outcomes are recruitment and retention.

**Results:**

Participants’ demographic and clinical characteristics are presented along with baseline data.

**Conclusions:**

Next Level has recruited to target, providing evidence that it is feasible to recruit to a RCT of MOL for first-episode psychosis.

## Background

People experiencing a first episode of psychosis (FEP) should have access to early intervention in psychosis (EIP) services that are capable of delivering appropriate psychological interventions, including cognitive–behavioural therapy for psychosis (CBTp).^1^^,^^2^ There is relatively good evidence to support the use of CBTp, with most meta-analyses estimating effect sizes in the small to moderate range.^3^^–^^5^ However, despite recommendations from the National Institute for Health and Care Excellence that everyone experiencing psychosis should be offered CBTp, levels of implementation have remained low.^6^^–^^8^ A recent audit of EIP services found that just 41% of patients had been offered CBTp and, of these, only 51% accepted the offer.^9^ Additionally, evidence from qualitative studies suggests that some patients find CBTp ‘difficult to engage with’ and ‘emotionally difficult’.^10^^,^^11^ There is also evidence that CBTp has only modest benefits over other ‘generic’ interventions for people experiencing psychosis, such as befriending and supportive counselling.^4^

There are high levels of comorbidity among people who experience psychosis, including problems with anxiety, depression, post-traumatic stress disorder and substance misuse.^12^^–^^16^ This presents challenges for clinicians aiming to deliver disorder-specific interventions for psychosis. Where individuals prioritise non-psychotic difficulties, CBTp practitioners will draw on relevant, compatible approaches to inform treatment.^17^ However, clinicians require suitable training and supervision in the application of these approaches. There is also good evidence that transdiagnostic cognitive and behavioural processes maintain psychological distress across diagnostic categories.^18^^,^^19^ Interventions that specifically target transdiagnostic processes might have advantages over disorder-specific approaches in terms of efficiency^20^ and the extent to which they meet the complex needs of people who experience psychosis.^21^^,^^22^

Some researchers have advocated focusing on single symptoms of psychosis (such as persecutory delusions) and targeting the mechanisms proposed to be maintaining them (for example worry, reasoning biases).^23^^,^^24^ Here we present an alternative approach to psychotherapy that targets goal conflict, a core mechanism proposed to maintain psychological distress across diagnostic categories, irrespective of the exact symptoms or problems reported by individuals.

## Method of levels

The method of levels (MOL) is a transdiagnostic cognitive therapy that has been well described in a number of treatment manuals.^25^^–^^27^ MOL aims to help people shift their awareness onto the conflicted goals that are believed to be maintaining distress. Sustaining awareness on the conflict facilitates an innate learning process called reorganisation, which enables people to resolve goal conflict. Therapists delivering MOL have two goals: (a) to encourage the person to talk freely about their problems, and (b) to pay attention for ‘disruptions’ and, when they occur, ask about these. Disruptions are indications that the person's awareness has fleetingly shifted onto potentially relevant background thoughts. Examples would include interruptions to the flow of speech, smiling or laughing, and evaluative statements (such as ‘That sounds silly’).

MOL has several potential advantages over existing psychological approaches for psychosis. These include: it is applicable to individuals presenting with multiple problems simultaneously; it aims to give people greater choice and control over the interventions they receive; treatment is tailored to meet their individual needs; it is based on clear principles derived from a robust scientific theory of human behaviour (see below for more details); it has the potential to use psychological resources more efficiently; and it aims to directly target the factor that is proposed to maintain psychological distress.

## Study aims

To summarise, although CBTp is the current ‘gold standard’ psychological intervention for individuals using EIP services, there are significant difficulties with its implementation in routine clinical practice, as well as queries about how effectively and efficiently it is meeting the psychological needs of this population. MOL is an innovative and promising psychological therapy for FEP. It has several potential advantages over existing treatments and warrants further evaluation.^21^^,^^22^ No previous trials of MOL for FEP have been conducted, so it is necessary to establish the feasibility of recruitment and retention before a full efficacy trial could be justified.

This study aims to answer four research questions.
Is it feasible to recruit and retain people experiencing a first episode of psychosis in a randomised controlled trial (RCT) of MOL?Is MOL an acceptable psychological intervention for people experiencing FEP?Is it feasible to deliver MOL to people experiencing FEP?Are adaptations necessary to overcome problems or barriers to the implementation of MOL in EIP services?

## Method

Next Level is a parallel group feasibility RCT with two conditions: (a) treatment as usual (TAU) and (b) TAU plus MOL. The study was prospectively registered with the ISRCTN registry (trial registration ISRCTN13359355). As a feasibility trial, participants and their clinical team, the trial therapist and the outcome assessor are not masked to group allocation. If MOL appears suitable for further testing in an efficacy trial, outcome assessors would be masked to group allocation. A trial retention rate of 80% at final follow-up would be considered a successful outcome. The trial was designed with reference to the Medical Research Council's guidelines on developing and evaluating complex interventions.^28^ The trial is sponsored by the University of Manchester and is being conducted across two EIP services within Greater Manchester Mental Health NHS Foundation Trust. Participants randomised to TAU continue to receive support from their EIP team. Participants randomised to the treatment group receive MOL in addition to their usual care. A novel feature of this design is that participants in the treatment group are able to choose the number, frequency and duration of MOL sessions they access over the course of the treatment window. This approach is consistent with the underlying theoretical assumptions of MOL. A nested qualitative study is also included in the design.

### Trial oversight and ethical approval

A trial steering committee (TSC) comprising clinical, academic and patient members has been convened to oversee the study. As a small feasibility study, it was not deemed necessary to establish a separate data monitoring and ethics committee. Instead, the TSC also served some of the functions normally carried out by a data monitoring and ethics committee. The independent members of the TSC had the option to meet independently of the research team if required.

Ethical approval was received from the North West – Greater Manchester Central Research Ethics Committee prior to commencing recruitment (REC reference: 16/NW/0592; IRAS project ID: 204043).

### Randomisation

Following baseline assessments, participants were randomised by [name] to one of the two conditions in a ratio of 1:1. An online randomisation service (Sealed Envelope Ltd, 2017, https://www.sealedenvelope.com/simple-randomiser/v1/) was used to allocate participants in random permuted blocks. There was no stratification of the study sample. To minimise the potential for bias, participants were randomised in the order they completed baseline assessments.

### Sample size

A formal power calculation was not performed, since the aim of the study is not to estimate between-group treatment effects. A sample size of 15 participants or more in each group is considered adequate for a feasibility RCT.^29^ To allow for potential attrition, the recruitment target was 36 participants.

### Recruitment

Participants were recruited from two EIP services based in a single National Health Service (NHS) trust in the UK. Participants were either experiencing or recovering from a recent FEP. Care coordinators within those teams were asked to raise awareness of the study among patients on their case-loads. Presentations, posters and leaflets were used to provide study information to care coordinators. Individuals who expressed an interest in the study were contacted via telephone by the chief investigator. If verbal consent was given at this point, patients were invited to meet the chief investigator in person to receive information about the study, complete a brief eligibility screen and provide written consent to participate in the study prior to the completion of baseline assessments. Participants were made aware of their right to withdraw from the study at any time.

### Inclusion criteria

People aged 16–65 years.Current user of Greater Manchester Mental Health NHS Foundation Trust early intervention services.Sufficient English language abilities (verbal and written) to complete written material (for example, outcome measures) and participate in psychological therapy.Willing and able to provide informed consent.

### Exclusion criteria

People aged under 16 or over 65 years of age.Not currently using Greater Manchester Mental Health NHS Foundation Trust early intervention services.Literacy or English language difficulties that make it difficult for the person to complete written material (for example, outcome measures) or to participate in psychological therapy.Individuals currently serving custodial prison sentences.

### Eligibility and outcome measures

A brief screen consisting of the inclusion and exclusion criteria was used to ensure eligibility. A summary of the assessment schedule is presented in the Appendix. Assessments in both arms were completed by the chief investigator, who was not masked to group allocation.

The proposed primary clinical outcome measure for the purposes of estimating an effect size is the Psychological Outcome Profiles (PSYCHLOPS),^30^ a participant-generated outcome measure that assesses well-being, functioning and distress. Cronbach's alpha in a clinical sample was 0.81,^31^ demonstrating satisfactory internal reliability.

The CORE Outcome Measure (CORE-OM)^32^ is a 34-item self-report instrument that assesses the four domains of subjective well-being, symptoms, functioning and risk. It shows good sensitivity to change and has been used in a variety of practice settings. Cronbach's alpha in clinical samples was found to be 0.94, indicating satisfactory internal reliability.^32^

The Reorganisation of Conflict Scale (ROC)^33^ is a 22-item self-report measure. Each item is scored on a scale of 0 (‘I don't believe this at all’) to 100 (‘I believe this completely’). The study used an 11-item subscale of the ROC that has previously shown satisfactory internal reliability, with a Cronbach's alpha of 0.83.^34^ The subscale measures the components of goal conflict reorganisation, which is proposed to be the key mechanism of change in MOL.

The Questionnaire about the Process of Recovery (QPR)^35^ is a 22-item self-report questionnaire developed in collaboration with patients. It is designed to measure personal recovery from psychosis on two subscales: intrapersonal functioning and interpersonal functioning. Cronbach's alpha was found to be 0.94 for the intrapersonal scale and 0.77 for the interpersonal scale, indicating good internal consistency.^35^

The Outcome Rating Scale (ORS)^36^ is a visual analogue questionnaire that assesses functioning in four domains: individual, social, relational and overall functioning. It is scored from 0 to 40, with scores at or below 25 indicating clinically severe levels of psychological distress. Cronbach's alpha was found to be 0.93, indicating good internal consistency.^36^

The Session Rating Scale (SRS)^37^ is also a visual analogue scale. It assesses patients' perceptions of the therapeutic alliance, including the extent to which the participant felt respected and heard. As with the ORS, the SRS is scored from 0 to 40 with scores of 36 or below indicating cause for concern about the therapeutic alliance. Cronbach's alpha was found to be 0.88, indicating satisfactory internal consistency.^37^

### MOL intervention

MOL directly applies the principles of a robust theory of human behaviour called perceptual control theory (PCT) to the practice of psychotherapy. Detailed descriptions of PCT and its application to the delivery of psychological therapy are available.^38^^,^^39^ The proposed mechanism of change in MOL is the reorganisation of goal conflict. MOL therapists aim to guide a person's awareness onto the source of the conflict, facilitating this process. MOL is a transdiagnostic psychological intervention, which means it is applicable to individuals presenting with diverse problems, irrespective of any diagnosis they might have received. Sessions typically last between 15 and 60 min.

Because PCT proposes that change is non-linear and idiosyncratic,^27^ participants are expected to require a different number and frequency of sessions over the course of the 10-month treatment window. To support this, the study uses patient-led appointment scheduling, an approach that has already been used successfully with a secondary care population.^20^ MOL sessions will be offered at two community venues, one at each recruitment site. A total of five appointment slots will be made available each week at the site with higher levels of recruitment. The site with lower recruitment will have three appointment slots available each week. Capacity issues will be reviewed on an ongoing basis to monitor whether additional appointment slots are required. Participants allocated to receive MOL will be able to book the sessions they require using SMS (short message service) messages, telephone calls or a dedicated online appointment booking website. There is no minimum or maximum number of sessions that participants are expected to attend over the 10-month treatment window where sessions are available to them. Detailed descriptions of MOL and patient-led scheduling are available in several treatment manuals.^25^^–^^27^^,^^40^

The MOL sessions are delivered by the study's chief investigator, a suitably trained clinician with experience of delivering psychological interventions for psychosis. The clinician receives weekly supervision from experienced MOL practitioners. The MOL intervention is delivered according to the guidelines described in published treatment manuals.^25^^–^^27^ Audio recordings of MOL sessions are rated using the MOL Session Evaluation Form.^41^ To ensure fidelity to the approach, a randomly selected sample of MOL session audio recordings will be independently rated at the end of the trial. The intention is to rate 20% of audio recordings.

### Safety monitoring and reporting

Untoward occurrences that result in death, admission to hospital, disability, that are considered life threatening or are otherwise deemed medically significant will be recorded. Incidences of threatened or actual overdose, self-harm or harm to others will also be recorded. Potential adverse events are most likely to be identified at MOL sessions, assessments and qualitative interviews. In addition, participants' medical notes will be reviewed at the end of the trial to identify any other potential adverse events. In the first instance, the chief investigator, primary investigator and chair of the TSC will review potential adverse events to determine the appropriate response. All potential adverse events will be reviewed by the TSC.

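### Adverse events have an extra identification route in the TAU + MOL arm only, so a side-by-side comparison by arm may under-record TAU unless it rests on routes common to both arms

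*Protocol article*

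**What the plan says.** All references are to the protocol article.

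- Safety monitoring and reporting defines two groups of events. The first is serious outcomes: "Untoward occurrences that result in death, admission to hospital, disability, that are considered life threatening or are otherwise deemed medically significant will be recorded". The second depends more on what participants disclose: "Incidences of threatened or actual overdose, self-harm or harm to others will also be recorded".
- The same section names where events are expected to surface: "Potential adverse events are most likely to be identified at MOL sessions, assessments and qualitative interviews". It then adds a further route: "participants' medical notes will be reviewed at the end of the trial to identify any other potential adverse events". That review is not limited to one arm. All potential events go to the trial steering committee (TSC).
- Under Method, the arms differ in trial contact: "Participants randomised to the treatment group receive MOL in addition to their usual care", while "Participants randomised to TAU continue to receive support from their EIP team".
- Under MOL intervention, session numbers are left to the participant: "There is no minimum or maximum number of sessions that participants are expected to attend over the 10-month treatment window". The chief investigator delivers the sessions and, under Eligibility and outcome measures, also carries out the assessments in both arms without masking.
- The Appendix schedules outcome assessments at baseline, 10 and 14 months in both arms, and further measures at MOL sessions.

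**The concern.** One of the three places named as most likely to bring events to light is open to one arm only. A TAU + MOL participant who books sessions meets a member of the trial team repeatedly over 10 months. After baseline, a TAU participant's scheduled trial assessments are at months 10 and 14. Interviews may add to this, but the article does not say when they take place or in which arm.

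The events most exposed to this difference are those that rely on disclosure. A threat voiced in a therapy session can be recorded at once. The same threat in a TAU participant is recorded only if the early intervention team writes it down or the participant reports it months later.

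If events are then set out by arm, the difference mixes harm with intensity of observation. A small apparent excess under MOL could be read as harm, or a real excess could be dismissed as better detection. Neither reading could be checked without knowing how each event was found. The trial is meant to inform whether MOL goes forward to a definitive trial, so readers are likely to compare the arms whether or not the report does so formally.

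**Working it through.** **What the article fixes.** It states no event rate, detection rate or power figure, so there is no figure to reproduce. The routes by arm are:

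| Route | TAU + MOL (n = 19) | TAU (n = 17) |
|---|---|---|
| MOL sessions, over 10 months | yes, number chosen by participant, may be zero | no |
| Assessments at 10 and 14 months | yes | yes |
| Qualitative interviews | arm and timing not stated | arm and timing not stated |
| Medical notes review at trial end | yes | yes |

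**Illustrative model (all probabilities assumed).** Let the true event rate be the same in both arms and let the routes act independently. Let c be the chance that an event is picked up at assessments or interviews, m the chance that it is in the notes, and s the chance that it is picked up at a MOL session.

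- Recorded in TAU: 1 − (1 − c)(1 − m)
- Recorded in TAU + MOL: 1 − (1 − c)(1 − m)(1 − s)

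Worked case with c = 0.3, m = 0.5, s = 0.6:

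- TAU: 1 − 0.7 × 0.5 = 0.65
- TAU + MOL: 1 − 0.7 × 0.5 × 0.4 = 0.86
- Ratio: 0.86 / 0.65 = 1.32

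Across c = 0.3 to 0.6 and s = 0.3 to 0.9:

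| Notes capture m | Lowest ratio (c = 0.6, s = 0.3) | Highest ratio (c = 0.3, s = 0.9) |
|---|---|---|
| 0 (event never in the notes) | 0.720 / 0.600 = 1.20 | 0.930 / 0.300 = 3.10 |
| 0.5 | 0.860 / 0.800 = 1.075 | 0.965 / 0.650 = 1.48 |
| 0.8 | 0.944 / 0.920 = 1.03 | 0.986 / 0.860 = 1.15 |
| 0.95 | 0.986 / 0.980 = 1.01 | 0.9965 / 0.965 = 1.03 |
| 1 | 1.00 | 1.00 |

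The ratio is also 1.00 when s = 0. In this model it never falls below 1, so the distortion runs one way. Its size is governed mainly by how complete the notes are. The first row describes only events that never reach the notes. It is not the ratio for all events.

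**In numbers of events.** Assume 0.3 true events per participant and the worked case above.

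- Expected recorded events in TAU + MOL: 19 × 0.3 × 0.86 = 4.9
- Expected recorded events in TAU: 17 × 0.3 × 0.65 = 3.3
- TAU + MOL without the session route: 19 × 0.3 × 0.65 = 3.7

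The session route therefore adds about 4.9 − 3.7 = 1.2 events. The rest of the gap, 3.7 against 3.3, comes from arm size alone (19 / 17 = 1.12). Raw counts should not be compared for that reason as well.

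**The case against.** The strongest reply is that the article plans no comparison of adverse events by arm. The analyses it sets out cover recruitment, retention, session attendance, other therapies received, and regression on the outcome measures. The safety section describes recording and TSC review, which is oversight. None of the four research questions names safety, and the only numerical success thresholds concern retention. This stands: the problem arises only if events are set side by side by arm.

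A second reply is that the common routes do much of the work. TAU participants remain under their early intervention team, whose contact can generate notes, so they are not unobserved between assessments. Deaths, admissions and life-threatening events would be expected to reach the notes. This also stands, and it narrows the point to events that depend on disclosure.

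Several stronger readings are tempting, but the article does not support them:

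- That events are actively sought at sessions. The text says only that they are likely to come to light there, and describes no structured enquiry.
- That MOL counts will be inflated. Under unequal detection the MOL count is more complete, not above the truth. TAU is the arm that may fall short, and by how much is unknown.
- That events are pooled with no record of how they were found. The article does not say how events are logged, and a source field is the kind of detail an article leaves to fuller documents.
- That session contact is without limit. There is no set maximum per participant, but supply was 5 + 3 = 8 slots a week across the two sites, subject to review, and some participants were expected to attend none.

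A last reply is that removing session-only events from a comparison could hide distress that first appears in therapy. That is a fair warning. It is met by listing those events in full beside the comparative table.

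**Conclusion.** The point holds in a limited form. By the plan's own description, one identification route exists in one arm only. The notes review and the scheduled assessments reduce the resulting imbalance, possibly to nil for deaths and admissions. They reduce it less surely for threats or incidents that a participant mentions only in a session.

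The direction is clear if arms are compared: with equal true rates, TAU may be relatively under-recorded. The size cannot be derived from the article. The illustrative ratios of about 1.03 to 1.48, with 50% to 80% of events in the notes, rest on assumed detection probabilities, independent routes and equal true rates. In arms of 19 and 17, that may amount to an event or two.

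The documents do not support a conclusion that MOL will look harmful or that the safety data are unusable. This is a modest and inexpensive improvement to how events are tabulated and read.

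**What to change.** 1. Assign each recorded event its detection source: MOL session, scheduled assessment, qualitative interview or notes review. Where the source was not captured at the time, code it retrospectively from trial records. Where it cannot be traced, say so.
2. Base any between-arm statement on the routes common to both arms: the notes review over the same window from randomisation to 14 months, plus the scheduled assessments. Leave interviews out of this table unless they were held on the same terms in both arms.
3. Report proportions or rates, not raw counts, because the arms are 19 and 17.
4. List events found only at MOL sessions separately and in full, without comparing them with TAU.
5. Give both tables to the TSC, and state in the report that ascertainment differed between arms.

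The cost is some source coding after data collection has closed, one extra table, and fewer events in the comparative table. No event is dropped from the report, and no trial procedure changes.
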